#### Satisfaction of psychological needs

DRAMMA needs experiences are measured with a 16-item scale. Detachments, relaxation, autonomy and mastery dimensions are each measured with three items from the Recovery Experience Questionnaire [14]. In addition, four additional items were developed to measure meaning and affiliation. Example items are: “Over the past week, during time after work, I forgot about work” (detachment), “Over the past week, during time after work, I kicked back and relaxed” (relaxation), “Over the past week, during time after work, I determined for myself how I will spend my time” (autonomy), “Over the past week, during time after work, I did things that challenge me” (mastery), “Over the past week, during time after work, I experienced meaning in my life” (meaning), “Over the past week, during time after work, I experienced close connections to the people around me” (affiliation). Participants can indicate their agreement with the statements on a scale from 1 (I do not agree at all) to 5 (I fully agree).

#### Home demands

Home demands are measured with the Home Demands Scale [52]. The scale consists of three subscales: quantitative home demands (example item: “How often have you been busy at home over the past month?”), emotional home demands (example item: “How often did emotional issues arise at home over the past month?” and mental home demands (example item “How often did you have to do many things simultaneously at home over the past week?”). The scale used in this study consists of nine items with one original mental demands item excluded. Participants are asked to report their demands in private life over the past week with the answer range from 1 (never) to 5 (very often).

#### Job demands

During each measurement, participants are asked to report their past week’s working hours. Additionally, three types of job demands will be measured during each measurement. Workload is measured with three items from the Quantitative Workload Inventory [53]. An example question is: “How often did your job require you to work very fast over the past week?”. Cognitive job demands are measured with three questions from the Copenhagen Psychosocial Questionnaire [54] and the DISC Questionnaire [55]. An example item is: “How often did your work require that you remember a lot of things over the past week?”. Emotional job demands are measured with three items from the Copenhagen Psychosocial Questionnaire [54]. An example item is: “How often did your work evoke unpleasant feelings over the past week?”. The response scales for all job demand items ranges from 1 (very rarely or never) to 5 (very often or all the time).

#### Job crafting

Job crafting is measured with a 4-item job crafting scale [56]. An example item is: “I change my job so it would better fit with who I am”. Participants are asked to respond on a 5-point Likert scale from 1 (very rarely or never) to 5 (very often).

#### Off-job activities

Off-job activities are measured with a newly developed scale. The scale is composed of various scales which have previously been used to measure participation in different leisure activities [57–61]. Participants can indicate the frequency of engaging in different leisure activities (e.g., active socializing, cultural activities, outdoor activities) on a scale from 1 (almost never) to 5 (several times a day).

#### Proactive personality

Proactive personality is measured only with the baseline questionnaire, using a six-item version of the Proactive Personality Scale [62]. An example item is: “I excel at identifying opportunities”. Employees can choose a response from 1 (totally disagree) to 5 (totally agree).

#### Focus on opportunities

Focus on opportunities is measured in the baseline questionnaire with a four-item scale [63]. An example item is: “My occupational future is filled with possibilities”. Participants can reply on a scale from 1 (does not apply at all) to 5 (applies completely).

#### Selection, optimization and compensation strategies

Selection, Optimization and Compensation strategies are measured in the baseline questionnaire with a twelve-item scale [63]. The scale has four subscales: elective selection (example item: “At work, I concentrate all my energy on few things”), loss-based selection (example item: “When things at work don’t go as well as they have in the past, I choose one or two important goals”), optimization (example item: “At work, I make every effort to achieve a given goal”), and compensation (example item: “When things at work don’t go as well as they used to, I keep trying other ways until I can achieve the same result I used to”). Participants can reply on a scale from 1 (does not apply at all) to 5 (applies completely).

#### Background variables

We ask the participants to state their age, gender, highest level of formal education, family status, living situation, type of work, weekly working hours, and tenure.

### Statistical analyses

#### Sample size calculation

The G*POWER software [64] was used to determine the minimum number of participants necessary to guarantee sufficient power of the study. Assuming an effect size of .25 (medium), alpha = .05 and power = .80, the required sample size is 64 participants per group to determine a significant difference between the intervention and the waitlist control group. Taking into account potential non-response and loss to follow-up, we aim to recruit at least 200 employees to ensure an adequate sample size.

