**Fig. 1 Fig1:**
[figure not shown]
Off-job crafting intervention design

The study will be carried out in Finland from October 2019 to May 2020. All participants who have given informed consent to participate in the study will first fill out an online baseline questionnaire, concerning demographics (e.g., age, gender, education), basic job information (e.g., work hours), off-job and job crafting, psychological needs, well-being (e.g., mental fatigue, work engagement) and performance (e.g., family role performance, organizational citizenship behavior) 2 weeks before the intervention period. Additionally, intervention group participants will receive a small task to complete before the first training session. The task consists of composing a list of things that the participant likes and dislikes doing during their off-job time. In addition, they are asked to take two picture that represent: 1) an activity that they loved doing over the past week and 2) an activity that they did not like to do during their off-job time. One week before the first training session, participants will receive a reminder to complete the questionnaire and the homework task. Two weeks after the baseline measurement, intervention group participants will take part in a half-day long training session. Shortly before the training, each intervention group participant receives a personal feedback report containing information about their baseline scores on DRAMMA needs satisfaction and comparison of their scores to reference values derived from other published scientific studies with Finnish and European knowledge workers as the reference group [23–25]. During the four-week intervention period, every Tuesday, intervention group participants will receive an email with a link to a weekly online questionnaire. In case of non-response, reminders will be sent on Wednesdays and Thursdays. The control group will be asked to fill out a second questionnaire immediately after the end of the intervention period of the intervention group. Additionally, participants from both groups will receive the same online questionnaire via email twice during the post-intervention period (two and six weeks after intervention). After the intervention period, the intervention group will participate in a half-day long reflection session.

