#### Basic analyses

All basic analyses are carried out with SPSS 25 [65]. Two-tailed significance level of < .05 will be considered statistically significant. Baseline characteristics of the participants are analyzed using descriptive statistics. Independent samples t-tests or chi-square tests are applied to check whether randomization was successful or whether there were systematic differences between the two groups. Preliminary analysis will be performed, including calculating descriptive statistics (i.e., means, standards deviations), factor analyses for all the scales, internal reliability calculations (Cronbach’s *α*) and bivariate correlations (Pearson’s *r*) between the study variables.

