#### Effect evaluation

We will use multilevel modelling techniques to test the change in outcome variables within subjects across seven measurement points before, during and after the intervention (i.e., within subject effect of participating in off-job crafting intervention). We will use Bliese and Ployhart’s [66] approach to estimate multilevel models in R, using the NLME library written by Pinheiro and Bates [67]. Additionally, we will test how participation in off-job intervention compared to control group affects the change in outcome variables across time (i.e., between subjects’ effect of the intervention compared to control group).

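### The 64 per group fits a one-time two-group comparison, so its 0.80 power is not shown to apply to the planned test of a group difference in change

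*Protocol article*

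**What the plan says.** Under Sample size calculation, the protocol article gives the inputs as "Assuming an effect size of .25 (medium), alpha = .05 and power = .80" and concludes that "the required sample size is 64 participants per group to determine a significant difference between the intervention and the waitlist control group". It names no effect-size metric, time point, number of measurements or within-person correlation. To allow for non-response and loss to follow-up it adds: "we aim to recruit at least 200 employees to ensure an adequate sample size". Basic analyses sets the test level: "Two-tailed significance level of < .05 will be considered statistically significant".

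Effect evaluation plans multilevel models to "test the change in outcome variables within subjects across seven measurement points before, during and after the intervention". For the comparison between arms it says: "we will test how participation in off-job intervention compared to control group affects the change in outcome variables across time". It does not describe how time is coded or how the baseline value enters the model.

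Study design shows that the arms do not share all seven occasions. The weekly questionnaires go to the intervention group. For the controls: "The control group will be asked to fill out a second questionnaire immediately after the end of the intervention period of the intervention group". Both arms are then measured two and six weeks after the intervention. The shared occasions are therefore baseline, end of intervention and the two follow-ups. Measures states that every questionnaire carries all the outcomes, so each outcome has a baseline value, although off-job crafting uses 18 items at baseline and 6 afterwards.

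**The concern.** The sample size and the planned test do not visibly refer to the same quantity. A comparison of two groups at one time needs only the standardised difference. A comparison of change subtracts the baseline measurement, which adds its noise and removes the stable part of each person's score. Whether that gains or loses power depends on how strongly repeated measurements correlate.

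If correlations are modest, 64 per group can fall short of 0.80 for the between-group test. Several outcomes are single items (stress, health status, private life and job satisfaction, job performance), mostly with one-week recall. Modest correlations are conceivable there, but the article gives no values.

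**Working it through.** **Inputs.** From the article: effect size .25, alpha .05 two-sided, 64 per group. Assumed: d = 0.50 on the raw SD (set to 1); equal correlation r between any two occasions of one person (compound symmetry, i.e. a random intercept). All values of r are assumptions.

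**1. The stated figure.** With two groups d = 2f = 2 × 0.25 = 0.50. A two-sided two-sample t-test (noncentral t) at d = 0.50 needs 64 per group, with power 0.801. This reproduces the article. Read as d, .25 would need 253 per group. Repeated-measures ANOVA options at f = .25 and correlation 0.5 do not give 128 in total: for 2, 4 or 7 measurements the group-by-time interaction gives 34, 24 or 18, and the between-group factor gives 98, 82 or 74.

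**2. Contrasts of change.** Let V be the per-person variance of the tested contrast. The effective standardised difference is 0.50/√V, so power matches the stated 0.80 when V ≤ 1.

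- Single pre-post change: V = 2(1 − r). V = 1 at r = 0.5.
- Linear slope over the four shared occasions. Baseline is two weeks before a four-week intervention, so these fall at about weeks 0, 6, 8 and 12. Mean time is 26/4 = 6.5 and the sum of squared deviations is 244 − 676/4 = 75. With d = 0.50 reached at week 12, V = 144(1 − r)/75 = 1.92(1 − r). V = 1 at r = 1 − 1/1.92 = 0.48.
- Average of three post waves minus baseline, constant effect: V = (1 − r)(1 + 1/3). V = 1 at r = 0.25.

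**3. The same contrasts with baseline used efficiently.**

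- Single post wave, baseline as covariate: V = 1 − r².
- Slope with equal baseline means: V = 144(1 − r)/(244 − 676r/(1 + 3r)). At r = 0.3 this is 100.8/(244 − 106.7) = 0.734.
- Average of three post waves, baseline as covariate: V = (1 + 2r)/3 − r². At r = 0.3 this is 0.533 − 0.09 = 0.443.

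**4. Power at 64 per group (noncentral t).**

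| Contrast | r = 0.3 | r = 0.4 | r = 0.5 |
|---|---|---|---|
| Single change | 0.66 | 0.73 | 0.80 |
| Single post, adjusted | 0.84 | 0.86 | 0.90 |
| Slope, four occasions | 0.68 | 0.74 | 0.82 |
| Slope, equal baseline means | 0.91 | 0.91 | 0.93 |
| Average of three post − baseline | 0.83 | 0.88 | 0.93 |
| Average of three post, adjusted | 0.99 | 0.99 | 0.99 |

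At r = 0.3 the single change needs 89 per group for 0.80 power and its adjusted counterpart 59. For r between 0 and 1 the adjusted V never exceeds 1 (single post), about 0.73 (slope) or 0.44 (average), so power does not fall below 0.80 in these forms.

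**5. Sensitivity.** Adding the weekly intervention-arm data lowers the threshold for the average-post contrast to about 0.20, and a slope fitted to those data has power 0.72 at r = 0.3 and 0.78 at 0.4. With correlation decaying by week (AR(1)) in place of compound symmetry, the average-post contrast including those data has power 0.76 when the baseline to week-6 correlation is 0.26, and 0.88 when it is 0.53.

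**The case against.** A reader might infer that the stated power holds only if the correlation is at least 0.5. The article does not support that. The 0.5 threshold is exact for one baseline and one post measurement, whereas the plan is a multilevel model with several post-baseline measurements. For the average of three post waves the threshold is about half that.

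A reader might also infer that 64 can come only from a one-time comparison and that the stated power must belong to a different test. That is too strong. With f = .25 and one numerator degree of freedom, 128 in total also results for two groups with one covariate, and a t-test on change scores standardised to 0.50 on the change SD also needs 64 per group. If .25 was meant on the scale of the change, the calculation needs no correlation. This stands as a possibility, but nothing in the article says so.

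The article's silence on baseline handling is not a decision against adjustment. A test of group on change is valid under randomisation and compatible with equal baseline means. The full analysis plan may settle this.

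Finally, at least 200 are to be recruited. With 80 per group analysed (20% loss, assumed) even the single change score has power 0.76 at r = 0.3 and 0.82 at 0.4; with 100 per group it has 0.85 at 0.3. This softens the consequence. But the article sets the surplus aside for non-response and loss: 128/200 leaves room for 36% loss, and 64 remains the stated requirement.

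**Conclusion.** The point holds in limited form. The 64 per group matches a one-time comparison at d = 0.50. The between-group test is a difference in change, and the article gives neither a correlation nor a contrast to connect the two, so 0.80 is not shown to be the power of the planned test.

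With d = 0.50 on the raw SD and 64 per group, the correlation needed for 0.80 runs from about 0.25 (average of three post waves, compound symmetry) through just under 0.5 (linear slope, random intercept) to 0.5 (single change score). Whether there is a real shortfall depends on the contrast, the covariance structure and correlations that are assumed here. A conclusion that the trial is underpowered would go beyond the article. Efficient use of the baseline raised power in each of the three forms at the correlations tabulated and kept it at or above 0.80, so the change is worth making whatever the true correlations are.

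**What to change.** In Effect evaluation, state that the between-group effect is estimated at the post-baseline waves with the same outcome's baseline value as covariate, or in a mixed model with baseline means constrained equal across the randomised arms.

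In Sample size calculation, name the effect-size metric (Cohen's f, if that is what was used) and the contrast and time point or points it applies to. Restate power for that contrast over a stated range of correlations.

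The cost is wording in two sections and one model term or constraint. No further participants or measurements are needed, because every outcome is already measured at baseline.

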#### Basic analyses

All basic analyses are carried out with SPSS 25 [65]. Two-tailed significance level of < .05 will be considered statistically significant. Baseline characteristics of the participants are analyzed using descriptive statistics. Independent samples t-tests or chi-square tests are applied to check whether randomization was successful or whether there were systematic differences between the two groups. Preliminary analysis will be performed, including calculating descriptive statistics (i.e., means, standards deviations), factor analyses for all the scales, internal reliability calculations (Cronbach’s *α*) and bivariate correlations (Pearson’s *r*) between the study variables.

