The aim of this intervention study is to evaluate the effectiveness of a hybrid off-job crafting intervention compared to a waitlist control group on off-job crafting behaviors, psychological need satisfaction, well-being and performance. We hypothesize that off-job crafting can be stimulated in the intervention group compared to a waitlist control group (between-person difference), and that people will engage more often in off-job crafting during and after the intervention period than before (within-person changes). Moreover, we expect that increased off-job crafting will lead to higher well-being and performance during and after the intervention (compared to baseline and to the control group). We hypothesize that as the result of the intervention, participants will report higher basic need satisfaction and satisfaction of psychological needs during and after the intervention compared to baseline and to the waitlist control group. In terms of work-related well-being outcomes, we expect that participants will report higher work engagement and job satisfaction during and after the intervention compared to baseline and to the waitlist control group. In the non-work domain, we hypothesize that participants will report higher subjective vitality, private life satisfaction and health status and lower stress and mental fatigue levels during and after the intervention compared to baseline and to the waitlist control group. We also expect the intervention to have a positive effect on both work-related and non-work performance. Namely, we expect participants to report higher job performance and organizational citizenship behavior at work and increased family role performance in the non-work domain during and after the intervention compared to baseline and to the waitlist control group. Additionally, we will explore, whether variables such as proactive personality, focus on opportunities, selection, optimization, and compensation strategies, need strengths, home and job demands, job crafting and off-job time activities have a role in participants’ engagement in different off-job crafting behaviors and its effects to their well-being and performance in different life domains.

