### Study population and recruitment

The study population is recruited from diverse private and public organizations in the capital region and Pirkanmaa region in Finland. The participants are full-time employees with knowledge-intensive jobs. The contacted organizations have previously been interested in Tampere University recovery studies or belong to the network of the trainers delivering the intervention. We will first contact the organizations’ HR representatives by sending them an informational recruitment letter, followed by follow-up calls. Individual informational meetings with interested companies will be arranged.

After the company has agreed to participate in the study, we will forward our recruitment email to their employees. This email includes additional information about the study, including the timeline of the intervention. An organization can take part in the study if there are at least 12 employees interested in participating in the study. In each participating organization, a person will be appointed to facilitate the communication between participants, trainers, and researchers. This person will also provide the employees with a registration form (requesting employee’s name and contact information). Within each organization, we aim to assign participants randomly either to the intervention or to the waitlist control group. After the intervention, employers will receive an anonymized group feedback regarding the development of participants’ levels of stress, mental fatigue, job performance and organizational citizenship behavior across different measurement points.

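### Thirteen hypothesised outcomes, none named primary, share an unadjusted .05 threshold, and the sample size is built for a single comparison tied to no outcome

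*Protocol article*

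**What the plan says.** The aim in the Background section is to evaluate the intervention "compared to a waitlist control group on off-job crafting behaviors, psychological need satisfaction, well-being and performance". The hypotheses follow, starting with "We hypothesize that off-job crafting can be stimulated in the intervention group compared to a waitlist control group". Counting every outcome given a directional hypothesis there yields 13:

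- off-job crafting
- basic need satisfaction and satisfaction of psychological needs
- work engagement and job satisfaction
- vitality, private life satisfaction, health status, stress and mental fatigue
- job performance, organizational citizenship behavior and family role performance

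The article gives no order among them, names none as primary and states no rule for calling the intervention effective.

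The Sample size calculation section reads "Assuming an effect size of .25 (medium), alpha = .05 and power = .80", and concludes that "the required sample size is 64 participants per group" for a difference between the two arms. It names no outcome. It then adds a margin for losses: "we aim to recruit at least 200 employees to ensure an adequate sample size".

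The Basic analyses section states: "Two-tailed significance level of < .05 will be considered statistically significant". The Effect evaluation section describes multilevel models of change over time, within subjects and between groups, for the outcome variables as a block. It states no alpha of its own.

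**The concern.** A sample size calculation belongs to a particular hypothesis. Here the 80% power attaches to none, so a reader of the results cannot tell which comparison the trial was designed to answer. With 13 co-equal hypotheses and one unadjusted threshold, emphasis can settle after the fact on whichever outcomes reach significance, and the error rate for the set is well above the nominal 5%. The choice of primary outcome belongs in the protocol and is not a detail normally left to the analysis plan.

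**Working it through.** **Inputs from the article.** Effect size .25 labelled medium, alpha .05, power .80, 64 per group and a target of at least 200 (Sample size calculation); two-tailed .05 (Basic analyses); 13 outcomes (Background). The allocation ratio is not stated. I assume 1:1, which fits 64 per group.

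**Step 1: reproduce the 64.** The value .25 is the conventional medium value of Cohen's f. For two equal groups d = 2f = 2 × 0.25 = 0.5. The normal approximation gives n = 2 × (1.96 + 0.84)² / 0.5² ≈ 63 per group. The exact two-sided t test, and equivalently the two-group ANOVA with f = .25, gives 64 per group with power 0.801. The figure is therefore one two-group test at alpha .05. Read as d, .25 would need 253 per group, so the metric should be named.

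**Step 2: familywise error for 13 tests, one per outcome, no true effects.**

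- Independent, either direction: 1 − 0.95^13 = 0.487.
- Independent, hypothesised direction only (.025 each): 1 − 0.975^13 = 0.280.

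The outcomes are self-reports from the same people, so they will correlate. The article gives no correlations, so these are assumptions. Test statistics were simulated as equicorrelated standard normals (200,000 draws), counting any value beyond 1.96:

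| Assumed correlation | Any false positive | False favourable result |
|---|---|---|
| 0 (exact) | 48.7% | 28.0% |
| 0.3 | 41.7% | 21.3% |
| 0.5 | 33.4% | 16.7% |
| 0.8 | 19.2% | 9.5% |

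**Step 3: what treating all 13 as co-equal would cost.** Bonferroni sets alpha at 0.05/13 = 0.00385, and the familywise error under independence becomes 1 − (1 − 0.00385)^13 = 4.9%. At d = 0.5, 80% power per outcome then needs 114 per group, or 228 completers, which exceeds the target of 200. Power per outcome is 46% with 64 per group, and 73% with 100 per group and no losses. With one named primary outcome, alpha stays at .05 and 64 per group suffices. The target of 200 then allows a loss of up to 1 − 128/200 = 36%.

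**Step 4: the time dimension, conditional only.** Under Study design, the control group answers after baseline at the end of the intervention period and at two and six weeks, so at most three post-baseline times allow a between-group comparison. If each outcome were tested separately at all three (13 × 3 = 39 tests), the chance of any false positive would be 1 − 0.95^39 = 86% under independence. It would be about 60–76% with assumed correlations of 0.3–0.5 between outcomes and 0.5–0.7 between times. Effect evaluation does not say that this will be done.

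**The case against.** Several objections have force.

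- **The threshold.** The .05 sentence sits under Basic analyses, beside randomisation checks, factor analyses and correlations. The effect models come in a separate section with no alpha. This stands: carrying .05 over is an inference. It is a reasonable one, since the sample size calculation uses the same alpha and the article offers no other.
- **Time points.** A reader might infer that every outcome is tested at every wave, making 39 contrasts. The document does not support this. Effect evaluation describes a model of change across time, so the 39-test figures show only what would follow from a choice the article does not state.
- **Likelihood.** A reader might also conclude that a false verdict of effectiveness is likely. For 13 tests the chance of any false positive is below one half even under independence. The hypotheses are directional, so the favourable-direction figures, 28% at most, are the closer measure. Nor does the article say that one significant outcome would make the intervention effective.
- **The count.** Measures places both need-satisfaction scales under potential moderators, mediators and control variables. Without them 11 outcomes remain, and the independence figure is 1 − 0.95^11 = 43%. The Background hypotheses still treat both as outcomes, and the conclusion does not change.
- **Condensed article.** An adjustment procedure may sit in an analysis plan that is not shown, so its absence is not the finding. That does not excuse a sample size attached to no outcome.
- **Bonferroni.** It is conservative, and 64 per group is the minimum rather than the target. The 46% therefore illustrates the cost of one correction and does not forecast the trial's power.

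**Conclusion.** The point holds. The article hypothesises effects on 13 outcomes, ranks none, and sizes the trial for one unnamed two-group comparison. If each between-group effect is tested once at .05, the chance of at least one false-positive result is up to 49% under independence, and about 19–42% under assumed correlations of 0.8–0.3. For a false favourable result it is about 9.5–28%. All are above the level that one pre-named test would carry: 5%, or 2.5% in the favourable direction. These figures rest on no true effects, one test per outcome, equal correlations that I have assumed, and the inference that .05 governs the effect tests. The supported conclusion is a materially inflated error rate and a power statement without an owner. The 64 itself is arithmetically correct.

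**What to change.** Add a paragraph to Statistical analyses that names one primary outcome, one time point or time contrast, and the between-group comparison, tested at two-sided .05. State that the 64 per group refers to that comparison and that .25 is Cohen's f.

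Off-job crafting is a natural candidate, being the first hypothesis and the programme's direct target. It would have to be scored on the same six items at every wave, because the article uses 18 items at baseline and six afterwards. The investigators may prefer a well-being or performance outcome, since those are also in the aim.

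The time point needs a stated reason. At the end of the intervention, the intervention group completes its last weekly questionnaire during the on-site second training session, while controls answer a separate questionnaire after the intervention period. At two and six weeks both arms receive the same questionnaire by email.

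Treat the other 12 outcomes as secondary, either with a multiplicity adjustment such as Holm or false-discovery control, or labelled exploratory. Say whether times will be tested separately.

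The cost is one paragraph, with no change to recruitment or data collection. The downside is that fewer secondary results will count as confirmed.
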